# Fluid hydration to prevent post-ERCP pancreatitis in average- to high-risk patients receiving prophylactic rectal NSAIDs (FLUYT trial): study protocol for a randomized controlled trial

**DOI:** 10.1186/s13063-018-2583-x

**Published:** 2018-04-02

**Keywords:** Post-ERCP pancreatitis, Prevention, ERCP, Hydration, NSAIDs

## Abstract

**Background:**

Post-endoscopic retrograde cholangiopancreatography (ERCP) pancreatitis (PEP) is the most common complication of ERCP and may run a severe course. Evidence suggests that vigorous periprocedural hydration can prevent PEP, but studies to date have significant methodological drawbacks. Importantly, evidence for its added value in patients already receiving prophylactic rectal non-steroidal anti-inflammatory drugs (NSAIDs) is lacking and the cost-effectiveness of the approach has not been investigated. We hypothesize that combination therapy of rectal NSAIDs and periprocedural hydration would significantly lower the incidence of post-ERCP pancreatitis compared to rectal NSAIDs alone in moderate- to high-risk patients undergoing ERCP.

**Methods:**

The FLUYT trial is a multicenter, parallel group, open label, superiority randomized controlled trial. A total of 826 moderate- to high-risk patients undergoing ERCP that receive prophylactic rectal NSAIDs will be randomized to a control group (no fluids or normal saline with a maximum of 1.5 mL/kg/h and 3 L/24 h) or intervention group (lactated Ringer’s solution with 20 mL/kg over 60 min at start of ERCP, followed by 3 mL/kg/h for 8 h thereafter). The primary endpoint is the incidence of post-ERCP pancreatitis. Secondary endpoints include PEP severity, hydration-related complications, and cost-effectiveness.

**Discussion:**

The FLUYT trial design, including hydration schedule, fluid type, and sample size, maximize its power of identifying a potential difference in post-ERCP pancreatitis incidence in patients receiving prophylactic rectal NSAIDs.

**Trial registration:**

EudraCT: 2015-000829-37. Registered on 18 February 2015.

ISRCTN: 13659155. Registered on 18 May 2015.

**Electronic supplementary material:**

The online version of this article (10.1186/s13063-018-2583-x) contains supplementary material, which is available to authorized users.

## Background

Endoscopic retrograde cholangiopancreatography (ERCP) is widely used to treat diseases of the pancreaticobiliary tree. The most frequent complication is post-ERCP pancreatitis (PEP) [1]. The reported overall incidence varies from 7% to 10% and approaches 15% in high-risk patients [2]. In the United States, costs related to PEP are estimated to be over $200 million annually [3].

Numerous prophylactic measures for PEP have been investigated [4]. However, the evidence is indisputable for only two measures – rectal non-steroidal anti-inflammatory drugs (NSAIDs) and prophylactic pancreatic duct (PD) stents. Recent meta-analyses calculated an odds ratio of 0.44 for rectal NSAIDs [5] and 0.35 for PD stents [6]. Therefore, the American Society for Gastrointestinal Endoscopy recommends the use of rectal NSAIDs and PD stents in high-risk patients and suggests the use of rectal NSAIDs in average-risk patients [7]. The European Society for Gastrointestinal Endoscopy (ESGE) recommends routine use of rectal NSAIDs in all patients undergoing ERCP, while reserving PD stents for high-risk patients [4].

A new promising prophylactic strategy for PEP is periprocedural hydration. It is intended to preserve adequate pancreatic perfusion and tissue oxygenation during ERCP. The strategy finds its justification in the theory that early pancreatic microcirculatory perfusion derangements are correlated with severity of acute pancreatitis [8]. Circumstantial evidence supporting this theory is that an increased level of pre-procedural blood urea nitrogen, a marker of hemoconcentration, has been associated with PEP development and severity [9, 10]. Many patients subjected to ERCP are fasting and may therefore be relatively dehydrated. Furthermore, a retrospective cohort study found an inverse relationship between peri-ERCP hydration and PEP severity [11].

A recent meta-analysis on periprocedural hydration [12], including seven RCTs with 1047 patients, showed an odds ratio of 0.47 (0.30–0.72; *P* = 0.0006) in favor of protection against PEP. There was no significant difference in adverse events between the intervention and control groups (*P* = 0.23). However, the included RCTs had several shortcomings, the most important of which being that patients did not receive rectal NSAIDs – these cannot be withheld from patients due to the clear evidence in favor of their use [13]. Furthermore, a synergistic effect of hydration and rectal NSAIDs is plausible because both act at a different stage of PEP development; hydration preserves pancreatic microcirculation and NSAIDs suppress the inflammatory response.

The FLUYT trial is designed to investigate whether periprocedural hydration with lactated Ringer’s solution can prevent post-ERCP pancreatitis in moderate- to high-risk patients undergoing ERCP who already receive prophylactic rectal NSAIDs.

## Methods

The trial protocol is written in accordance with the SPIRIT guidelines (Fig. 1, Additional file 1) [14].

**Fig. 1 Fig1:**
[figure not shown]
SPIRIT schedule of enrolment, interventions, and assessments. *Baseline variables: age, sex, comorbidity, American Society of Anesthesiologists score, ERCP indication, PEP risk factors, use of pancreatic duct stents. ^Primary outcome: post-ERCP pancreatitis. ^#^Secondary outcomes: incidence of delayed PEP (> 24 h after ERCP), severity of PEP, other ERCP complications, hydration-related complications, length of hospital and intensive care unit stay, health-related quality of life, cost-effectiveness, and exocrine and endocrine pancreatic insufficiency

### Study setting

The FLUYT trial is a multicenter, parallel group, open label, superiority randomized controlled trial that will include 826 patients from 20 hospitals of the Dutch Pancreatitis Study Group, including 3 university medical centres and 17 large teaching hospitals (see ‘Participating Centers’ at the end of the protocol for more details).

### Eligibility criteria

Patients aged 18–85 years undergoing ERCP and who provide written informed consent are included in the study.

The exclusion criteria are as follows:Low risk of post-ERCP pancreatitis: (1) definite chronic pancreatitis according to MANNHEIM criteria [15], (2) previous sphincterotomy, (3) pancreatic head mass, and (4) routine biliary stent exchange. In case of a pancreatic duct intervention, chronic pancreatitis and previous sphincterotomy are not exclusion criteriaAcute pancreatitisAltered anatomy, defined as anatomical variations in which bile and/or pancreatic secretions (in case of pancreatic duct interventions) do not enter the duodenum by way of the ampulla of Vater (e.g., Roux-en-Y reconstruction, surgery for chronic pancreatitis)PregnancySigns of congestive heart failure, such as pitting edema or a New York Heart Association classification greater than class I heart failureRespiratory insufficiency (pO_2_ < 60 mmHg or saturation < 90% despite FiO_2_ of 30% or requiring mechanical ventilation)Severe liver disease (cirrhosis and ascites)Patients receiving more than 1.5 mL/kg/h or 3 L/24 h of intravenous fluids in the 24 h before ERCPHypotension (systolic blood pressure < 90 mmHg or mean arterial pressure < 70 mmHg)Hypo- or hypernatremia (serum Na^+^ levels < 130 or > 150 mmol/L)Contraindications for rectal NSAIDs, including allergy, active gastrointestinal bleeding, ulcer disease, renal insufficiency (glomerular filtration rate < 30 mL/min) and NSAID use for other indications (other than cardioprotective aspirin)

### Treatment arms and co-interventions

Eligibility of all potential participants will be discussed with the central study coordinator. After written informed consent, patients are randomized to either the control or intervention group. The control group will be administered 100 mg of indomethacin or diclofenac within 30 min before or after ERCP and no hydration or mild hydration with normal saline, with a maximum of 1.5 mL/kg/h or 3 L/24 h;. After 24 h, the volume and nature of intravenous infusion is at the discretion of the treating physician. The intervention group will be administered 100 mg of indomethacin or diclofenac within 30 min before or after ERCP and periprocedural hydration with lactated Ringer’s solution, 20 mL/kg within 60 min from the start of ERCP (endoscope-mouth contact), directly followed by 3 mL/kg/h for 8 h. Thereafter, the volume and nature of intravenous infusion is at the discretion of the treating physician.

The type, dosing, and timing of rectal NSAID application follow the recommendations of the ESGE [4]. Current ERCP guidelines give no indication for hydration in the control group. Therefore, the hydration schedules in both the intervention and control group are based on the favorable results seen in Buxbaum’s pilot study [16].

To ensure timely delivery of the 60 min bolus, pressure bags or double infusion pumps will be used. The hydration is maximized in patients with morbid obesity (body mass index > 40), because their altered physiology is characterized by a decrease of lean body in tissue water content [17]. Therefore, in these patients, a maximum amount of fluid is calculated by using a fictive maximum weight (FMW) associated with a body mass index of 40 kg/m^2^. The FMW is calculated as follows:$$ FMW=40\ {\left( patient\ length\ in\ meters\right)}^2 $$

The FMW is inserted in the fluid equations of the intervention group.

If the clinical condition of patients in the control group does not allow the infusion restrictions (e.g., in case of hypovolemic shock), higher volume infusion is allowed at the discretion of the treating physician. Furthermore, if patients in the intervention group develop signs of fluid overload, the intensive hydration will be stopped and, if needed, diuretics will be started.

General treatment measures include a fasting state before ERCP. Antibiotic prophylaxis, measures to correct coagulation disorders and diet reintroduction after endoscopic sphincterotomy will be managed according to a local protocol. We did not encourage the use of pancreatic duct stents to prevent confounding with the intensive hydration regimen. After ERCP, all patients will be hospitalized for a minimum stay of 24 h for timely diagnosis of adverse events and monitoring of intravenous fluid volumes. Longer monitoring, hospitalization, and treatment of adverse events is at the discretion of the treating physician. Post-ERCP pancreatitis will be treated in accordance with the International Association of Pancreatology/American Pancreatic Association guidelines for treatment of acute pancreatitis [18].

To improve adherence to the trial protocol, involved staff members (gastroenterologists, residents, physician assistants, endoscopy nurses, ward nurses and sedationists) in all participating centres will receive specific training in the trial’s standard operating procedures (SOPs). In coordination with the local principal investigator, the SOPs are adapted to the local hospital setting, while ensuring adherence to the trial protocol. Furthermore, the SOPs will be readily available on all wards and on the dedicated FLUYT trial website. The trial coordinator is on call 24/7 to assist in case of any questions. Protocol adherence is evaluated regularly in participating centres.

### Outcomes

The primary outcome is the incidence of post-ERCP pancreatitis according to the Cotton criteria [19]. The criteria of (1) new onset upper abdominal pain; (2) elevation of pancreatic enzymes (amylase and/or lipase) to more than three times the institutional upper limit of normal; (3) criteria 1 and 2 are present at least 24 h after ERCP; and (4) hospitalization (or extension of planned admission) for at least 2 nights, must all be present.

The secondary endpoints (Additional file 1) are (1) incidence of delayed PEP (PEP occurring > 24 h after the procedure); (2) severity of PEP – this will be reported according to the Cotton criteria [19] and the revised Atlanta criteria [20] since the severity grading differs between the two classifications [21, 22] and both are reported in studies; (3) ERCP-related complications according to the Cotton criteria [19], namely bleeding, perforation, and infection; (4) hydration-related complications, such as pulmonary edema and congestive heart failure; (5) length of hospital and intensive care unit stay; (6) generic health-related quality of life, measured by the EQ-5D and SF-36 [23, 24]; (7) cost-effectiveness; and (8) exocrine (fecal elastase-1 < 200 μg/L) and endocrine (HbA1c > 42 mmol/L) pancreatic insufficiency.

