### Sample size calculation

A recent meta-analysis [25] reported an 8% PEP incidence in patients receiving prophylactic rectal NSAIDs. We believe periprocedural hydration is a useful addition to rectal NSAIDs if it has a similar relative risk reduction of 60% [25, 26]. This minimal clinically important difference will cause the incidence of PEP to decrease from 8% in the control group to 3.2% in the intervention group, with a 4.8% absolute risk reduction. With a two-sided significance level of 5% and a power of 80%, a total of 718 patients (359 per treatment arm) is required to demonstrate this effect. To account for drop-out and missing data, we increased the sample size by 15%. This amounts to a final number of 826 patients (413 per treatment arm).

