### Data collection methods and follow-up

Clinical data are collected locally on standardized digital case record forms (CRFs) before ERCP, directly afterwards and in the 24 h thereafter. CRFs were created for the endoscopist, nursing staff, and treating physician on which to score the occurrence of the primary and secondary endpoints. Endoscopy and ward nurses will monitor all intravenous fluid infusion during the first 24 h after ERCP. After 24 h, the treating physician will assess the primary endpoint (abdominal pain suggestive of PEP) and blood is drawn for measurement of serum amylase and lipase. To ensure data quality, the central study coordinator will check all CRFs and contact responsible staff members in case of inconsistencies.

All patients are followed up for 180 days after randomization. Patients are contacted by telephone after 30, 90, and 180 days by a trial nurse. The validated EQ-5D, SF-36, and iMTA PCQ questionnaires for measuring quality of life and indirect non-medical costs will be sent simultaneously by (e-)mail, with a telephone reminder after a week if there is no response [23, 24, 27]. After 1 month of non-response, another telephone reminder will follow and a new questionnaire will be sent. In case of hospitalization, patients will be interviewed by a ward nurse. If patients experienced post-ERCP pancreatitis, pancreatic function will be assessed at 180 days post-randomization by fecal elastase and serum HbA1c measurements.

Unblinded, independent monitors will visit participating sites yearly for source document verification of 10% of the CRFs, including all components of the primary endpoint. If inconsistencies are encountered, all CRFs will be inspected.

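### The HbA1c cut-off for endocrine insufficiency is printed in a unit that makes it unattainable, and the fecal elastase unit also needs checking (secondary endpoint 8)

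*Protocol article*

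**What the plan says.** The protocol article lists eight secondary endpoints under Outcomes. The last is defined by two numeric cut-offs: "exocrine (fecal elastase-1 < 200 μg/L) and endocrine (HbA1c > 42 mmol/L) pancreatic insufficiency".

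Under Data collection methods and follow-up, the article says who is measured and how. In patients who had post-ERCP pancreatitis (PEP), "pancreatic function will be assessed at 180 days post-randomization by fecal elastase and serum HbA1c measurements". No units are given there. The legend to Fig. 1 repeats the endpoint by name only ("cost-effectiveness, and exocrine and endocrine pancreatic insufficiency").

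No other section of the article gives a cut-off or a unit for either test, so nothing in the text at hand corrects the printed ones.

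**The concern.** A cut-off decides who counts as having the outcome, so its unit is part of the rule. HbA1c is glycated haemoglobin. It is usable as a fraction of haemoglobin (mmol per mol, or per cent), whereas mmol/L is a concentration in blood. A threshold of 42 in that unit looks higher than any blood sample could reach. Fecal elastase is measured in stool, for which a per-litre unit is out of place. The follow-up section also calls the HbA1c sample serum, although HbA1c sits in red cells, which serum does not contain.

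At stake is whether endpoint 8 can be classified by the rule stated in advance. If the rule cannot be applied as printed, someone must supply another unit. Should that happen with results in hand, the classification is no longer pre-specified. The number of patients tested is small, so a few changed classifications would be visible in the comparison.

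**Working it through.** **Inputs from the protocol article**
- Endocrine cut-off: "endocrine (HbA1c > 42 mmol/L) pancreatic insufficiency" (Outcomes).
- Exocrine cut-off: elastase-1 below 200 μg/L (Outcomes).
- Tested population: patients with PEP, at 180 days (Data collection methods and follow-up).
- Planned PEP rates: "decrease from 8% in the control group to 3.2% in the intervention group", with 413 patients per arm after inflation (Sample size calculation).

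**Assumptions not in the article**
- Haemoglobin 70 to 250 g/L, a deliberately wide range.
- Molar mass of haemoglobin 16.1 g/mmol per chain, or 64.5 g/mmol for the four-chain molecule.
- Stool density 0.9 to 1.1 kg/L.

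**The plan's own figure.** The article gives no calculation for endpoint 8. Its sample size does reproduce: 8% against 3.2%, two-sided 5%, 80% power, without continuity correction, gives 359 per arm and 718 in total. Then 718 × 1.15 = 825.7, or 826. The point below does not depend on it.

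**Step 1: can HbA1c exceed 42 mmol/L?** HbA1c cannot exceed total haemoglobin, which is (g/L) ÷ (g/mmol).

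| Haemoglobin | Per chain | Four-chain molecule | 42 ÷ per-chain total |
|---|---|---|---|
| 70 g/L | 70 ÷ 16.1 = 4.35 mmol/L | 70 ÷ 64.5 = 1.09 mmol/L | 9.7 |
| 150 g/L | 9.32 mmol/L | 2.33 mmol/L | 4.5 |
| 250 g/L | 15.53 mmol/L | 3.88 mmol/L | 2.7 |

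The per-chain count is the one kinder to the plan, and the cut-off still lies above all the haemoglobin present in every row. For 42 mmol/L to be reached with every chain glycated, haemoglobin would have to be 42 × 16.1 = 676 g/L per chain, or 42 × 64.5 = 2709 g/L for the four-chain molecule. Neither is possible.

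**Step 2: the same number as a fraction.** 42 mmol/mol is 4.2% of haemoglobin. Per chain this is 0.042 × 4.35 = 0.18 mmol/L to 0.042 × 15.53 = 0.65 mmol/L, a range that can be met.

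**Step 3: elastase.** Read as per litre of stool, 200 μg/L is 200 ÷ 1100 = 0.18 to 200 ÷ 900 = 0.22 μg per gram. Conversely, 200 μg/g is 200 × 900 = 180,000 to 200 × 1100 = 220,000 μg/L, which is 900 to 1100 times the printed figure. The criterion is an upper limit, so a stool with almost no elastase would still satisfy it.

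**Step 4: how many patients.** 0.08 × 413 = 33 in the control arm and 0.032 × 413 = 13 in the intervention arm, together 46 of 826 (46 ÷ 826 = 5.6%).

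**The case against.** The strongest case on the other side is that this is a printing slip with little consequence.

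- **Who decides.** Under Blinding, a blinded adjudication committee works from primary source data and decides whether the endpoint definitions are met. Experienced clinicians reading laboratory reports would recognize the intended unit, and a single committee makes divergent site-by-site readings unlikely. This largely stands. The article does not support a picture of a central office applying the printed number mechanically to results from 20 hospitals. What remains is that the committee is asked to apply pre-specified definitions, and this one cannot be applied as printed.
- **Where the error sits.** The article refers to Additional file 1 for the secondary endpoints and to protocol version 3. Neither is at hand, and the slip may exist only in the article. This stands, and it is why the fix begins with a check.
- **The elastase figure.** The article does not say per litre of what, and it nowhere states a per-gram cut-off. The factor of about 1000 is therefore conditional on an inferred intention. This stands.
- **The specimen.** Calling the HbA1c sample serum changes no classification rule. It is a minor wording slip.

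A reader might go further and infer that endpoint 8 as a whole could never be met, so that both arms would show zero insufficiency whatever the truth. The text does not support that. The endpoint has two components, and the exocrine one is a less-than criterion that a near-zero result would meet. Only the endocrine component is out of reach.

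**Conclusion.** The concern holds for the units, with a limited effect. The endocrine cut-off is impossible as printed: it is 2.7 to 9.7 times all the haemoglobin in blood on the per-chain count at an assumed 70 to 250 g/L, and no plausible haemoglobin value changes that. The elastase unit does not suit stool. If a per-gram cut-off was meant, it is about 1000 times too strict but not unattainable. That mmol/mol and μg/g were meant is an inference, since the article does not state it.

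The consequence is confined to one secondary endpoint in about 46 patients at the planned rates. Literal application is a possibility and not a forecast of what the committee would do. The primary endpoint, its analysis, the interim analysis and the sample size are untouched. It is worth correcting because a stated decision threshold is wrong and the correction is cheap.

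**What to change.** 1. Check the intended cut-offs and units in the full protocol and on the case record form.
2. Correct the Outcomes section accordingly, presumably to HbA1c > 42 mmol/mol and fecal elastase-1 < 200 μg/g stool, before this endpoint is adjudicated and analyzed.
3. Make the case record form fields for both tests carry these units, so that a result reported in another unit is noticed on entry.
4. In Data collection methods and follow-up, drop the word serum before HbA1c.

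The cost is one line in the endpoint definition, one word in the follow-up section and a check of the form. No new measurement is needed. The article reports 515 of 826 patients randomized, with recruitment expected to last until the end of 2019, so at that stage the correction could still precede the final analysis.

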### Sample size calculation

A recent meta-analysis [25] reported an 8% PEP incidence in patients receiving prophylactic rectal NSAIDs. We believe periprocedural hydration is a useful addition to rectal NSAIDs if it has a similar relative risk reduction of 60% [25, 26]. This minimal clinically important difference will cause the incidence of PEP to decrease from 8% in the control group to 3.2% in the intervention group, with a 4.8% absolute risk reduction. With a two-sided significance level of 5% and a power of 80%, a total of 718 patients (359 per treatment arm) is required to demonstrate this effect. To account for drop-out and missing data, we increased the sample size by 15%. This amounts to a final number of 826 patients (413 per treatment arm).

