### Randomization

Patients are randomized centrally by the study coordinator in a 1:1 ratio by using a web-based randomization module. Participants were stratified by center. Within each stratum, random block sizes of 2, 4, and 6 were used. Due to the large sample size, age and sex are expected to be distributed equally between the groups. Therefore, no additional strata are used.

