#### Primary analysis

The primary endpoint will be analyzed according to the intention-to-treat principle with the use of Fisher’s exact test. That is, all randomized patients will be analyzed according to their original treatment allocation, regardless of study protocol violations. The only patients excluded from the analysis will be those in whom the duodenum was not reached and the papilla was not manipulated (e.g., in case of upper gastrointestinal stenosis, aspiration risk, restless patients). Because these patients did not have an ERCP, there is no risk of PEP. Comparison of the primary endpoint will be expressed in terms of a relative risk and 95% confidence intervals. An exploratory per-protocol analysis will also be performed. Reasons for protocol violations will be described. In these analyses we will not adjust for stratification by site. A two-tailed *P* value of less than 0.05 is considered to be statistically significant.

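### The stated 80% power at 359 per arm does not hold for Fisher's exact test, the named primary test, which gives about 77% at that size

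*Protocol article*

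**What the plan says.** Protocol article, Sample size calculation: the control rate comes from a meta-analysis that "reported an 8% PEP incidence in patients receiving prophylactic rectal NSAIDs". The target effect is a "decrease from 8% in the control group to 3.2% in the intervention group, with a 4.8% absolute risk reduction". The section then states: "With a two-sided significance level of 5% and a power of 80%, a total of 718 patients (359 per treatment arm) is required" to show this effect. It continues: "To account for drop-out and missing data, we increased the sample size by 15" per cent, which gives 826 patients, or 413 per arm. It names neither the test nor the formula behind 718.

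Protocol article, Primary analysis: "The primary endpoint will be analyzed according to the intention-to-treat principle with the use of Fisher’s exact test". A two-tailed P "value of less than 0.05 is considered to be statistically significant". The primary comparison is not adjusted for site.

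Protocol article, Randomization: "Patients are randomized centrally by the study coordinator in a 1:1 ratio".

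**The concern.** A power statement belongs to a particular test. Fisher's exact test conditions on the total number of events. With few events its attainable significance levels are coarse, so it rejects less often than an uncorrected chi-square test on the same data. If 359 per arm was derived for the chi-square test, the claim of 80% power does not carry over to the test that will decide the trial.

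At stake is a design property that the article relies on. Its Discussion criticises earlier trials for low power, claims adequate power for this one, and lists sample size among the choices that maximize power. The 15% increase is assigned to drop-out and missing data, so it was not set aside to pay for a conservative test.

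**Working it through.** **Inputs.** From Sample size calculation: p1 = 0.08, p2 = 0.032, two-sided alpha 0.05, power 80%, 359 per arm, 413 per arm after inflation. From Randomization: 1:1 allocation. From Primary analysis: Fisher's exact test, two-tailed, threshold 0.05.

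**Step 1: reproduce 359.** The pooled normal formula without continuity correction is

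n = [z(0.975) × √(2p̄(1−p̄)) + z(0.80) × √(p1(1−p1) + p2(1−p2))]² / (p1−p2)²

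- p̄ = (0.08 + 0.032)/2 = 0.056, and 2 × 0.056 × 0.944 = 0.105728, with square root 0.32516
- 0.08 × 0.92 + 0.032 × 0.968 = 0.0736 + 0.030976 = 0.104576, with square root 0.32338
- numerator: (1.95996 × 0.32516 + 0.84162 × 0.32338)² = (0.63730 + 0.27217)² = 0.82712
- denominator: 0.048² = 0.002304
- n = 358.995, so 359 per arm and 718 in total

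This matches the stated figure exactly. Other formulas give, per arm, 357 (unpooled variance, also uncorrected), 400 (continuity-corrected), 344 (arcsine), 391 (log relative risk) and 385 (log odds ratio). The pooled uncorrected formula is therefore the likely source, but this is an inference.

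**Step 2: exact power of the named test.** For every pair of event counts (x, y), compute the two-sided Fisher P as the sum of the probabilities of all tables with the same margins that are no more probable than the observed one. Power is the sum of Bin(x; n, 0.08) × Bin(y; n, 0.032) over all pairs with P ≤ 0.05. The chi-square and mid-P tests are handled in the same way.

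| Evaluable per arm | Fisher | Uncorrected chi-square | Mid-P |
|---|---|---|---|
| 351 (826 less 15%) | 75.6% | 80.6% | not computed |
| 359 (stated requirement) | 76.7% | 81.5% | 80.9% |
| 385 | 79.96% | 83.7% | not computed |
| 386 | 80.1% | not computed | not computed |
| 413 (all 826) | 83.1% | 86.3% | 86.2% |

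The Fisher result at 359 does not depend on how 359 was derived. The shortfall against the stated figure is 80.0 − 76.7 = 3.3 points.

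**Step 3: size of Fisher's test.** At 359 per arm the actual two-sided type I error is 3.64% when both rates are 8% and 3.37% when both are 5.6%. The test is conservative, which explains the lost power.

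**Step 4: what the 826 patients provide.** Fisher's test needs 2 × 386 = 772 evaluable patients for 80%. The loss that leaves 772 is (826 − 772)/826 = 54/826 = 6.5%. A full 15% loss leaves 0.85 × 826 = 702, or 351 per arm, and 75.6% power. Of the gap from 80% to 75.6%, 3.3 points come from the test. The other 1.1 points (76.7 − 75.6) arise because multiplying by 1.15 leaves 351 rather than 359 per arm after a 15% loss.

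The interim boundary at P < 0.001 was not modelled. Its effect on final power is assumed negligible.

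**The case against.** The best reply is that nothing has been miscalculated. The figure 359 reproduces to the patient, sizing by a normal approximation and analysing with Fisher's test is common, and a condensed article may omit the formula. This stands as far as it goes: the defect is a mismatch between two sections, not a slip of arithmetic. It does not rescue the 80%, because both the power claim and the test are stated in the article.

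The second reply is that 826 are randomized, and Fisher's test reaches 80% if no more than about 6.5% are lost. Losses may be small: patients stay at least 24 h, pain and enzymes are assessed at that point, and the only patients excluded from the analysis are those whose duodenum was not reached and whose papilla was not manipulated. This also stands, and it is why the matter is modest. A reader might infer that the trial as a whole is underpowered. The documents do not support that, since the only loss figure given is the 15% allowance and actual losses are unknown.

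Third, Fisher's test is valid. Its conservatism protects type I error, and a significant result would stand. Preferring a less conservative test is a design choice, not the correction of an invalid one.

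Two further inferences should be resisted. One is that the P value and the confidence interval will conflict. The article says only: "Comparison of the primary endpoint will be expressed in terms of a relative risk and 95% confidence intervals". It names no interval method, and that detail is commonly left to the full protocol or analysis plan. Any discordance can be shown only by assuming a method such as a Wald interval. The other is that a site-stratified Cochran-Mantel-Haenszel test should replace Fisher's. That would not match an unstratified calculation, and it would reverse the explicit choice to leave the primary analysis unadjusted for site and adjust only in a sensitivity analysis.

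**Conclusion.** The point holds, at modest severity. At the stated 359 per arm the named primary test has 76.7% power, not 80%, and it needs about 386 per arm. Over the range of losses the plan allows for, Fisher power runs from about 76% (full 15% loss) to about 83% (no loss). Type I error is not inflated and the validity of the primary result is not in question.

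The power figures rest on the plan's own rates of 8% and 3.2%, equal arms, independent outcomes, the usual two-sided Fisher P, and no allowance for the interim look. The attribution of 359 to the uncorrected formula is inferred, but the conclusion does not need it.

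**What to change.** Preferred: keep Fisher's exact test and restate the sample size paragraph. It should name the formula used for 718 and give the power of Fisher's test as about 77% at 359 per arm, with 386 per arm (772 evaluable) needed for 80%, about 76% if 15% of the 826 are lost, and about 83% if all 826 are analysed. This changes no patient number, test or decision rule. The only cost is a slightly less favourable stated figure.

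Alternative: name an unstratified uncorrected chi-square test or a mid-P exact test as primary. At 359 per arm these give 81.5% and 80.9%, so the stated 80% would hold without more patients. This requires a documented amendment made before any unblinded comparison is seen. The article reports 515 patients already randomized in an open-label trial, which is past the 413 set for the interim analysis, and does not say whether that analysis has been done. A late move to a more powerful test could be read as post hoc, so the restatement is the safer course.
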